## Abstract

**Background:**

The emergence of new molecular targeted drugs provides new prospects for the treatment of advanced breast cancer; the future therapeutic trend includes chemotherapy combined with molecular targeted therapy. Apatinib mesylate, a novel, small anti-angiogenic agent, highly selectively inhibits the activity of vascular endothelial growth factor receptor-2 tyrosine kinase. Apatinib mesylate also blocks the signaling of vascular endothelial growth factor binding to its receptor, thereby strongly inhibiting tumor angiogenesis and exerting an anti-tumor effect. However, there have been no reports of a randomized controlled clinical trial of apatinib combined with vinorelbine for the treatment of triple-negative breast cancer (TNBC). We will compare the therapeutic effect of vinorelbine alone or in combination with apatinib mesylate, in patients with recurrent or metastatic TNBC in North China who have received at least two drug treatments, including anthracyclines and taxanes.

**Methods/analysis:**

This study is a triple-blind, randomized, placebo-controlled, parallel-group clinical trial. We plan to include 238 female patients with locally recurrent or metastatic TNBC, admitted to the Liaoning Cancer Hospital & Institute, Northeast China. All enrolled patients will be randomized to oral vinorelbine alone (40 mg, thrice a week (Mondays, Wednesdays, and Fridays) in each 3-week cycle), or in combination with oral apatinib mesylate (500 mg, once daily in each 3-week cycle). Radiographic assessment will be performed every 6 weeks for 36 weeks and every 9 weeks thereafter. The primary outcome is progression-free survival and secondary outcomes include overall survival, disease control rate, objective response rate, and incidence of adverse events at grades 3 and 4, as defined by the National Cancer Institute Common Toxicity Criteria Version 4.0. Outcome measures will be evaluated at baseline (< 2 weeks before starting treatment), every 6 weeks during treatment, and at 4 weeks and every 3 months after treatment discontinuation.

**Discussion:**

Based on the data from this trial, we hope to identify a treatment plan that is suitable for female patients with TNBC, who have been treated with anthracyclines and taxanes, in Northeast China.

**Trial registration:**

ClinicalTrials.gov: NCT03932526. Registered on 30 April 2019.

## Introduction

### Background

The International Agency for Research on Cancer predicts that the number of cancers in the future will increase at an annual rate of 3–5%. The incidence of cancer in low-income and middle-income countries is extremely higher than that in developed countries [1]. Breast cancer is one of the most highly prevalent malignant tumors, with approximately 13 million people newly diagnosed each year. With a mortality rate of 20–30%, breast cancer is a common cause of death among women, accounting for 400,000 deaths annually. In developing countries, breast cancer has become the leading cause of death in women [2].

Triple-negative breast cancer (TNBC) is a subtype of breast cancer with an absence of estrogen receptors (ER), progesterone receptors (PR), and human epidermal growth factor receptor 2 (HER-2). It accounts for 10–17% of all breast cancers [3], and is characterized by high heterogeneity, high invasiveness, low survival rate, early recurrence, and metastasis. There is a lack of effective treatment for TNBC, and the prognosis is poor [4, 5].

Despite significant advances in breast cancer treatment, approximately 15% of patients are diagnosed at an advanced stage of breast cancer. According to staging, grading, and choice of treatment, 20–80% of all patients with invasive breast cancer will eventually relapse and require subsequent treatment [6]. Chemotherapy is the main treatment for early and advanced breast cancer, and the most effective drugs include anthracyclines and taxanes [7]. However, the increasing use of anthracyclines and taxanes in the early stage of the disease makes the choice of a second-line therapy difficult, and drug resistance often limits the choice of treatment regimens [8]. Endocrine therapy, anti-HER-2 targeted therapy, and chemotherapy cannot achieve satisfactory outcomes in TNBC, as there is no corresponding hormone receptor or HER-2 expression.

Some progress has been made in the field of TNBC therapy with the use of immunological checkpoint inhibitors. PD-1 or PD-L1 monoclonal antibody, the most common immunological checkpoint inhibitor, which targets either PD-1 or PD-L1, can block this binding and boost the immune response against cancer cells. Currently, only PD-L1 monoclonal antibody - atezolizumab (Tecentriq®) and PD-1 monoclonal antibody - pembrolizumab (Keytruda®) have been approved for use by the US Food and Drug Administration (FDA). The combination of pembrolizumab plus chemotherapy as a neoadjuvant therapy for early TNBC can significantly improve pathologic complete remission [9]. Relative to chemotherapy, pembrolizumab is used as a second-line or third-line treatment for patients with metastatic TNBC, but it does not significantly improve overall survival (OS) [10].

Results from the IMpassion130 trial (a clinical, phase III, double-blind randomized trial reported in 2016 [11], with data updated in 2019 [12]) indicated that the combination of atezolizumab and albumin paclitaxel as a first-line treatment for advanced TNBC yielded better progression-free survival than the use of paclitaxel plus placebo.

Unfortunately, no approval has been given for clinical trials on checkpoint inhibitors for TNBC in China; furthermore, no such drug is available in clinical practice. Therefore, this study was designed to determine the effect of the combination of apatinib (a small-molecule, anti-angiogenic targeted drug) and vinorelbine (a semi-synthetic, vinblastine alkaloid antineoplastic drug), two types of drugs that have been used clinically in China, in the treatment of TNBC.

Combination chemotherapy with vascular endothelial growth factor (VEGF) and VEGF receptor (VEGFR) target inhibitors is one of the most promising regimens for advanced breast cancer [13]. Apatinib mesylate (Aitan) is a novel, small anti-angiogenic agent that highly selectively inhibits the activity of VEGFR-2 tyrosine kinase, and blocks the signaling of VEGF binding to its receptor. Thus, it strongly inhibits tumor angiogenesis and exerts anti-tumor effects. While the clinical use of apatinib in breast cancer has been reported, the relevant research has focused mainly on its safety and efficacy in breast cancer expressing different receptors [13, 14]. The administration of apatinib in patients with TNBC, at an initial dose of 750 mg/day, resulted in mean progression-free survival (mPFS) and mean OS (mOS) of 4.6 and 8.3 months, respectively. A smaller dose (500 mg/day) resulted in mPFS and mOS of 3.3 and 10.6 months, respectively [14]. In cases of advanced breast cancer, oral apatinib was used after first-line or second-line treatment failure. The objective response rate (ORR) was 40.0%, the disease control rate (DCR) was 75.0%, and the median time to progression (mTTP) was 12 months [13].

Vinorelbine is mainly used for the treatment of non-small cell lung cancer and metastatic breast cancer. A previous multicenter clinical trial [15] used vinorelbine combined with cisplatin, capecitabine, or tegafur for the treatment of recurrent and metastatic breast cancer that occurred after treatment with anthracyclines and taxanes. The effective rate was 61.0%, with a complete response (CR) of 4.9%. This combination therapy was highly effective for multiple and single metastatic lesions, and moreover, the therapeutic efficacy was better in multiple metastatic lesions. The short-term effect was fair, with tolerance to toxicity and good safety. Studies have reported the use of vinorelbine combined with 5-fluorouracil among patients with advanced metastatic breast cancer (following treatment failure with anthracycline/taxane), and an effective rate of 17.4–46.0% [16–18]. In patients with metastatic TNBC, vinorelbine or gemcitabine combined with cisplatin is preferred after anthracycline/taxane treatment failure. The objective response rates of the experimental group and the control group were 45.45% and 46.15%, respectively, and the DCRs in the two groups were 77.27% and 80.77%, respectively. In the experimental group, the time to progression (TTP) was 2.0–18.0 months, and the mTTP was 5.0 months (95% confidence interval (CI), 3.28–6.72). In the control group, the TTP was 1.8–18.5 months, with an mTTP of 5.2 months (95% CI, 3.33–7.07) [19].

### Study features and objectives

While previous cohort studies [13, 20, 21], retrospective observations [22–25], and case reports [26, 27] have addressed the clinical treatment of TNBC with apatinib or vinorelbine (Table 1), there have been no reports of a randomized, controlled clinical trial in North China. As *BRCA*-positive patients would have poor responses to the therapeutic methods designed in this study, *BRCA*-negative female patients with locally recurrent or metastatic TNBC, who have previously received anthracycline and taxane treatment, will be the target population in this trial. We will compare the therapeutic effect of vinorelbine used alone or in combination with apatinib mesylate, for the treatment of recurrent or metastatic TNBC, with the aim of providing clinical evidence for multi-line treatment options.

**Table 1 Tab1:** Recent clinical studies conducted within the past 5 years on treatment with apatinib or vinorelbine in patients with TNBC pretreated with chemotherapy or radiotherapy

Study	Design	Subjects	Assignment	Treatment	Outcome measures	Conclusion
Treatment with apatinib						
Hu et al. [13]	Phase II cohort study	84 patients previously treated with anthracycline and/or taxane: 25 in phase IIa trial: 59 in phase IIb trial	–	Phase IIa trial: apatinib, daily dose of 750 mg Phase IIb trial: apatinib, daily dose of 500 mg	ORR and CBR were 10.7% and 25.0%, respectively. Median PFS and OS were 3.3 and 10.6 months, respectively	An apatinib dose of 500 mg rather than 750 mg is the recommended starting dose for heavily pretreated patients with mTNBC with a measurable rate of partial response and PFS
Li et al. [22]	Retrospective analysis	44 patients with advanced TNBC with failed first-line or second-line therapy	Apatinib + capecitabine or capecitabine alone	Apatinib (500 mg) was orally administered daily on days 1–28 of each 4-week cycle and/or capecitabine (12,500 mg/m^2^) was orally taken twice daily for 14 days followed by a 7-day rest period until disease progression	PFS, ORR (CR + PR), DCR (CR + PR + SD), and toxicity For apatinib + capecitabine or capecitabine alone: PFS, 5.5, 3.5 months; ORR, 40.9%, 13.4%; DCR, 68.2%, 31.8%	Treatment with a combination of apatinib and capecitabine can achieve a better efficacy and similar rate of serious adverse events compared with capecitabine alone, as the third-line treatment for advanced TNBC
Hu et al. [26]	Case report	A female patient with stage IV TNBC. She had previously undergone whole-brain radiation therapy. Paclitaxel, platinum, UTD1, capecitabine, gemcitabine, vinorelbine, and single-agent apatinib were then administered as first-line to fifth-line therapies	–	Treatment with apatinib + CPT-11 + S-1 as the sixth-line therapy	Alleviation of the brain edema was achieved, and this was maintained for 7 months	Apatinib in combination with CPT-11 + S-1 to treat refractory BMs in a patient with TNBC
Zhou et al. [27]	Case report	A female patient with triple-negative spindle cell carcinoma	–	After treatment failure with bevacizumab combined with albumin-bound paclitaxel and cisplatin, the patient was treated with apatinib	Apatinib was more effective than bevacizumab for this patient	Apatinib is a safe and effective drug for treating advanced spindle cell breast carcinoma, especially in patients who have a prior experience of chemotherapy failure, or a poor physical condition
Treatment with vinorelbine						
Rodler et al. [20]	Phase I cohort study	50 patients with advanced TNBC	–	A 3 + 3 dose escalation design evaluated veliparib and vinorelbine, followed by veliparib monotherapy	Median PFS in 50 patients was 5.5 months	Veliparib (300 mg, twice daily) combined with cisplatin and vinorelbine is well-tolerated with encouraging response rates
Zhang et al. [21]	Prospective cohort study	44 patients with metastatic TNBC pretreated with anthracyclines and/or taxanes	–	Biweekly combination of vinorelbine and oxaliplatin (NVBOX)	ORR 31.6%, median PFS 4.3 months, OS 12.6 months	A biweekly NVBOX regimen is effective and well-tolerated as a second-line or third-line treatment for patients with mTNBC
Wang et al. [23]	Retrospective analysis	48 female patients with TNBC	–	Patients were given vinorelbine plus cisplatin (NP group, *n* = 22) or gemcitabine plus cisplatin (GP group, *n* = 26)	The ORR, DCR, and median TTP were 45.5%, 77.3%, and 5 months, respectively, in the NP group, and 46.2%, 80.8%, and 5.2 months, respectively, in the GP group A lower incidence of thrombocytopenia and rash, and a higher incidence of phlebitis was found in the NP group compared to the GP group	Both the NP and GP regimens are active and tolerated in cases of metastatic TNBC with anthracycline and/or taxane resistance. These regimens may be used as a salvage treatment for metastatic TNBC
Du et al. [24]	Retrospective analysis	48 patients with metastatic TNBC pretreated with anthracyclines and one taxane	–	22 patients were treated with vinorelbine plus platinum (NP), and 26 patients with vinorelbine plus capecitabine (NX)	Total: ORR, 20.8%; CBR, 43.8%; median PFS, 4.4 months; median OS, 15.5 months ORR and PFS were better in the NP arm versus NX	Vinorelbine-based combination chemotherapy shows moderate efficacy in the treatment of metastatic TNBC, and has manageable toxicity. The NP regimen shows potential superiority over the NX regimen.
Li et al. [25]	Retrospective analysis	41 patients with advanced TNBC (pretreated with anthracyclines and/or taxanes, before or after surgery) in whom disease progressed after a certain period of time	–	Treatment with vinorelbine plus platinum (NP) regimen	ORR, 34.1%; CR, 7.3%; partial response, 26.8%; stable disease, 34.1%; median OS, 18.9 months; PFS, 6.7 months	The NP regimen showed clinical activity in patients with metastatic TNBC, and the toxicity was acceptable and manageable

*PFS* median progression-free survival, *ORR* objective response rate, *DCR* disease control rate, *BM* brain metastasis, *TNBC* triple-negative breast cancer, *CBR* clinical benefit rate, *OS* overall survival, *CR* complete response, *PR* partial response, *SD* stable disease, *TTP* time to progression

## Methods and analysis

### Study design

This study is a triple-blind, randomized, placebo-controlled, parallel-group clinical trial. A sample of 238 female patients with recurrent or metastatic TNBC, who have been pretreated with at least one chemotherapy regimen (including anthracyclines and taxanes), will be recruited. The baseline characteristics, therapeutic schedules, and outcomes of enrolled patients will be documented and reported in accordance with the Consolidated Standards of Reporting Trials (CONSORT) statement [28]. Patient data in each center will be collected by an electronic data capture system.

All enrolled patients will be randomly assigned to receive either oral apatinib mesylate in combination with vinorelbine or oral vinorelbine plus placebo, until disease progression or other criteria indicate the need for the termination of drug administration. A schedule of enrollment, interventions, and assessments is shown in Fig. 1 and a trial flowchart is shown in Fig. 2. The study protocol follows the Standard Protocol Items: Recommendations for Interventional Trials (SPIRIT) guidance for protocol reporting (Additional file 1) [29].

**Fig. 1 Fig1:**
[figure not shown]
Standard Protocol Items: Recommendations for Interventional Trials (SPIRIT). Timepoint (t): -t1: baseline evaluations (conducted within 2 weeks of the start of protocol therapy); t0: random allocation; t1: during treatment (evaluations will be conducted every 6 weeks (two cycles)); t2: patients will be monitored for new or existing AEs at 4 weeks after treatment discontinuation; t3: follow up for survival will be monitored every 3 months after treatment discontinuation until patient death or study completion. *Eligible patients will be randomly assigned to receive either oral vinorelbine plus placebo (control group) or oral vinorelbine combined with apatinib mesylate (experimental group). ^a^ Concomitant medication includes opioid analgesics and new anticancer treatment. ^b^ Laboratory examinations include hematology (hemoglobin, white blood cell count, neutrophil count, and platelet count); blood biochemical tests (total bilirubin, alanine aminotransferase, aspartate aminotransferase, alkaline phosphatase, serum creatinine, total protein, Na^+^, K^+^, Mg^2+^, Cl^−^, Ca^2+^, urea, and pregnancy test (if applicable); and tumor marker detection (breast cancer-associated antigen CA153 and carcinoembryonic antigen). ECOG PS, Eastern Cooperative Oncology Group performance status; EORTC QLQ-C30, the European Organization for Research and Treatment of Cancer Quality of Life Questionnaire Core-30

**Fig. 2 Fig2:**
[figure not shown]
Schedule of enrollment, interventions, and assessments. ECOG PS, Eastern Cooperative Oncology Group performance status; EORTC QLQ-C30, version 3, the European Organization for Research and Treatment of Cancer Quality of Life Questionnaire Core-30; CT, computed tomography; MRI, magnetic resonance imaging

### Study participants

The study participants will be recruited from the Liaoning Cancer Hospital & Institute in Northeast China.

#### Inclusion criteria

The inclusion criteria are:Female patients with recurrent or metastatic TNBC, confirmed by histological or cytological examination.Age ≥ 18 years.At least one extracranial measurable site of disease according to Response Evaluation Criteria In Solid Tumors (RECIST) version 1.1 criteria [30] and an Eastern Cooperative Oncology Group performance status (ECOG-PS) score of 0–2.Expected survival ≥ 12 weeks.Negative for ER/PR: where ER < 1% indicates positive and PR < 1% indicates positive. Negative for HER-2 refers to: immunohistochemical analysis (IHC)1+ indicates HER-2 negative, IHC2+ indicates an uncertain case of HER-2, according to specific diagnostic criteria (the *Breast cancer HER-2 detection guide, 2014 edition*) [31]. Further, the in-situ hybridization (ISH) method will be used to detect HER-2 gene amplification for further diagnosis.All patients will be tested for bone marrow capacity, liver, and renal function within 7 days prior to enrollment, and will meet the following criteria:Routine blood test: absolute neutrophil (ANC) count ≥ 1.5 × 10^9^/L; hemoglobin ≥ 9.0 g/dL; platelet count ≥ 80 × 10^9^/L;Liver function: total bilirubin ≤ 1.5 times the upper limit of normal (ULN); alanine aminotransferase (ALT) and aspartate aminotransferase (AST) ≤ 2.5 × ULN (patients with liver metastasis ≤ 5 × ULN); alkaline phosphatase ≤ 4 × ULN;Renal function: serum creatinine ≤ 1.5 × ULN.Previous use of anthracyclines and/or taxanes.The medication history of vinorelbine meets one of the following conditions:No history of, or irregular vinorelbine use (the standard use of vinorelbine is defined based on the appropriate use of the medication as prescribed, for at least two cycles);Patients with advanced breast cancer, who receive a standardized regimen of vinorelbine for 6 months and have no cancer progression; they also have not used vinorelbine within 6 months prior to the first administration.Female patients of childbearing age must take adequate contraceptio, otherwise they must be proven to be infertile, that is:Patients over the age of 50 years are confirmed to have menstruation-deficient menopause for at least 12 months after stopping all exogenous hormone treatments;Under the age of 50 years; on this basis, it is also necessary to prove that the levels of progesterone and follicle stimulating hormone are in the postmenopausal range of the research institution;Women undergoing irreversible sterilization operations (hysterectomy, bilateral oophorectomy, bilateral salpingectomy, etc.) are negative for pregnancy and are not lactating before administration.No history of serious heart, lung, liver, or kidney diseases.Provision of written informed consent.

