### Criteria for re-administration/cycle delay

Patients who meet all of the following criteria can receive the planned treatment:Absolute neutrophil count (ANC) > 1500/mm^3^Platelets > 100,000/mm^3^Treatment related to non-hematologic toxicity has been eliminated at baseline or is at a level ≤ 1 (except for level-2 alopecia or level-2 fatigue)

If the patient cannot meet these criteria, the planned treatment will be delayed and the patient’s condition will be re-evaluated at least once a week.

Additional criteria for re-administration/cycle delay are as follows:The medication on the 8th day of each cycle cannot be delayed for longer than 1 week, otherwise, the patient will be withdrawn from the study. The time of medication administration in the next cycle will not change.In the case of failure to recover from treatment-related toxicity to baseline or level 1 (except level 2 and level-2 fatigue) within 3 weeks as scheduled (i.e., the start of each new cycle is delayed for over 21 days as compared with the scheduled time), the patient will be withdrawn from the trial.Patients can continue to use the drug, with the consent of the Sponsor, if the treatment is deemed to be effective.

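### Patients can enter with platelets of 80–100 × 10^9/L but be treated only above 100 × 10^9/L, with no baseline allowance; separately, two limits on cycle delay conflict (2 weeks against over 21 days)

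*Protocol article*

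**What the plan says.** **Platelets.** The protocol article, Inclusion criteria, requires a "platelet count ≥ 80 × 10^9^/L" within 7 days before enrollment. Under Criteria for re-administration/cycle delay, a patient must meet every listed condition to receive planned treatment, and one of them is "Platelets > 100,000/mm^3". The consequence of failing is stated: "If the patient cannot meet these criteria, the planned treatment will be delayed", and the patient's "condition will be re-evaluated at least once a week". The same list makes an allowance for baseline status, but only for non-hematologic toxicity: "Treatment related to non-hematologic toxicity has been eliminated at baseline or is at a level ≤ 1".

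**Neutrophils, for comparison.** Entry needs "absolute neutrophil (ANC) count ≥ 1.5 × 10^9^/L"; planned treatment needs "Absolute neutrophil count (ANC) > 1500/mm^3".

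**Maximum delay.** Two sections give a limit. Dose adjustment requires withdrawal from the trial when the next cycle is late by 2 weeks or more. Criteria for re-administration/cycle delay has its own rule, which begins "In the case of failure to recover from treatment-related toxicity to baseline or level 1" and leads to withdrawal only when the start of a new cycle is more than 21 days late.

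**The concern.** A continuation rule is meant to catch deterioration on treatment. Here the count needed to continue is higher than the count needed to enter, so the rule can stop a patient whose count has not changed. She was accepted by the protocol, has had no toxicity, and is still held until she exceeds a level that was never asked of her at screening.

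The second problem concerns patients who do have toxicity. If recovery takes between 2 and 3 weeks, one section removes the patient and the other keeps her. Staff following different sections would handle the same patient differently.

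What is at stake is drug exposure, avoidable removal of patients, and consistent conduct. It is not the type I error rate or the validity of the primary comparison.

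**Working it through.** The plan states no figure to reproduce here. The check is a unit conversion and a comparison of thresholds.

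**Step 1: common units.** 1 L = 10^6 mm^3.
- Platelets: 100,000/mm^3 × 10^6 = 100 × 10^9/L.
- Neutrophils: 1500/mm^3 × 10^6 = 1.5 × 10^9/L.

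**Step 2: apply both platelet rules to the same count.**

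| Platelets (× 10^9/L) | Entry (≥ 80) | Planned treatment (> 100) |
|---|---|---|
| 80 | pass | fail |
| 90 | pass | fail |
| 99 | pass | fail |
| 100 | pass | fail |
| 101 | pass | pass |

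Every count from 80 to 100 inclusive is eligible and leads to a delay. A patient at the entry limit needs a rise of more than 100/80 − 1 = 25% over her own baseline.

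**Step 3: is the gap specific to platelets?** For neutrophils, entry is ≥ 1.5 and treatment is > 1.5 × 10^9/L. These differ only at exactly 1.5, which is trivial. Platelets are the only count in both lists with a real gap.

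**Step 4: does another provision close the gap?**
- The baseline allowance is limited to non-hematologic toxicity.
- Table 3 lets vinorelbine resume at platelets above 50 × 10^9/L, but its platelet entry is triggered by a level 3 or 4 event. A patient steady at 80–100 is above Table 3's own restart level and does not trigger it.
- Growth factor support, under Concomitant medications, is permitted; it does not waive the criterion.
- Continuation with the sponsor's consent is discretionary and depends on treatment being judged effective; it is not a platelet allowance.

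**Step 5: cost of one delay.** Vinorelbine is given 3 times a week for 3 weeks, so 9 doses in 21 days. A one-week delay makes it 9 doses in 28 days: 21/28 = 75% of planned intensity for that cycle.

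**Step 6: the two delay limits, for treatment-related toxicity.**

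| Delay of next cycle (days) | Dose adjustment (≥ 14: withdraw) | Cycle-delay section (> 21: withdraw) |
|---|---|---|
| 13 | stay | stay |
| 14 | withdraw | stay |
| 21 | withdraw | stay |
| 22 | withdraw | withdraw |

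The rules disagree for delays of 14–21 days inclusive.

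**The case against.** The best defence is that the effect is small and errs on the cautious side. The rule is identical in both blinded arms, the primary analysis is by intention to treat, and the Follow up section still collects progression and survival after treatment stops. The band of counts is narrow and nobody can say how many patients fall in it. All of this stands and sets the severity. It does not reconcile the two platelet limits or the two delay limits, which are explicit statements in the current text and not details left to a fuller document.

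A reader might infer several stronger things that the documents do not support.

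- **That the platelet check stops her at every cycle start.** The scheduled on-treatment blood tests are every 6 weeks (two cycles). The cycle-delay section names no test schedule of its own. A count of repeated checks up to median progression-free survival would also describe patients who pass them, not the one held at the first.
- **That sponsor consent could never help because imaging comes too late.** The first scheduled on-treatment blood test and the first imaging both fall at 6 weeks, so a low count found there can be considered together with response.
- **That a patient with a stable low count must be withdrawn.** The 2-week clause names no cause, but its setting is drug toxicity. The over-21-day rule is expressly about treatment-related toxicity. Withdrawal of this patient is a possible reading only.
- **That Table 3 is a third conflicting limit.** It can be read as a rule for resuming after a listed interruption.

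**Conclusion.** The concern holds in two parts. First, the entry and treatment limits for platelets are inconsistent for counts of 80–100 × 10^9/L, and an eligible patient who stays in that range is delayed without treatment toxicity. Second, the two withdrawal limits conflict for toxicity delays of 14–21 days.

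The size is minor. The documents give no baseline platelet distribution and no expected frequency of delays, so the number affected cannot be derived for either part. A one-week delay costs a quarter of that cycle's vinorelbine intensity, in whichever arm the patient is. A reader might go on to infer bias between arms or a loss of power; nothing in the documents shows either.

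The platelet conclusion assumes that the cycle-delay criteria are applied as written and that her count stays in the entry range. The delay-limit conclusion assumes that both sections apply to the same toxicity-related delay of the next cycle.

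**What to change.** **Platelets: choose one, on clinical advice.**
1. Raise the entry limit to > 100 × 10^9/L. The cost is some additional screen failures, number unknown.
2. Keep the hold at > 100,000/mm^3 and add, as an alternative for patients enrolled at 80–100 × 10^9/L, recovery to the patient's own baseline. Enrollment is unaffected; the cost is that clinicians must accept dosing these patients at counts they already accept at entry.

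Lowering the hold to ≥ 80,000/mm^3 for everyone is not advised. It would relax a safety hold for all patients, including one who falls from a normal count to 80 on treatment.

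**Delay limit.** Set one maximum cycle delay for treatment-related toxicity and state it identically in Dose adjustment and in Criteria for re-administration/cycle delay.

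Both changes need a protocol amendment with ethics committee approval, and no new test or visit.
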